**Passive Phase**		
Log book Diary notes of passive observations on clinical impact. 0–12 months Clinical Champion		
**Sustainability Phase**		
Focus Groups	Best practices and intervention impact during the passive phase.	12-24 months
**Data Mixing**		
Semi-structured interviews with key providers.	Follow-up of emergent questions.	14-16 months
Semi-Structured interviews with selected patients.	Contextual factors that may have influenced patient behaviors.	18-24 months

### Qualitative data handling and analysis

Analysis of qualitative data will continue throughout the project. Immediately following each observed intervention session, observers will meet at the PCN and construct a composite field note of the event directly into one of the team computers. Field notes will be entered into NVIVO 10 software (QSR International, Burlington, Mass.) Interviews will be audio recorded, transcribed verbatim, and entered into NVIVO.

Thematic Analysis will be the primary qualitative analysis approach for this project [15-18]. Thematic analysis refers to the systematic search for and identification of common themes that are present in data (transcripts and field notes). The unit of analysis will be the healthcare practitioner. Inductive rather than predetermined coding was chosen in order to allow themes to emerge from the data itself and reflects an exploratory rather than explanatory approach.

All interview transcripts will be coded and compared by more than one individual to ensure reliability. A coding manual will clearly outline code definitions and use. A clear record of how themes were generated from raw data will be reviewed by all team members.

### Qualitative and quantitative data mixing

Qualitative data analysis will be conducted on an iterative base and informs the intervention. The quantitative data for the primary outcome measure, number of weight management visits/FTE, will be collected in a blinded fashion for the first 12 months. At this point, the primary outcome measure will be analyzed. The study team will then be un-blinded and results will be compared with those from the qualitative analysis. It is expected that themes emerging from qualitative data will be reflected in patterns of quantitative data. Any correlation, or lack thereof, will be explored using key informant semi-structured interviews and focus groups. The purpose of this parallel mixed methods design is fourfold: first, to avoid bias during qualitative analysis; second, to explain any variability of the primary outcome measure; third, to record elements of RE-AIM not captured in the quantitative measures for the different providers in the intervention group; and fourth, to monitor the impact of context, and implementation process in part allowing for real-time feedback loops to maximize effective implementation.

### Patient-level study

The 5AsT patient portion of the study occurs concurrently with the provider study. Figure 1 (lower) details the patient-level study.

### Hypotheses

1. Implementation of the 5AsT in primary care, in addition to PCN weight management programs, will improve patient important outcomes: primary measures (weight, body mass index [BMI], Short Form 12-item Health Survey [SF-12]) and secondary measures (blood pressure [BP], waist circumference [WC], EuroQol EQ-5D [EQ-5D^TM^], modified Patient Assessment of Chronic Illness Care [PACIC] [19-22] and completion of recommended biomedical testing for those age > 40 or diabetic).

2. Activated patients, as defined as those who have elected to participate in PCN programming for weight management, will have improvement in patient-important outcomes with PCN programming.

3. Patients who attend 5AsT intervention practices will see improved sustained results greater than in those who attend practices that have standard PCN programming alone.

### Qualitative primary question

What contextual factors affect patient perception of in-clinic weight management efforts?

### Subject recruitment

A key feature of pragmatic trials is that the participants reflect the population for which the treatment is intended. For the widest generalizability, it is therefore essential that exclusion criteria be kept to a minimum. Inclusion criteria will be all adult patients older than 18 years with a BMI ≥25, enrolling in PCN programs for health, able and willing to give written informed consent in English. Children and pregnant women will be excluded. Since this is a trial of the primary care management of obesity, patients whose obesity is co-managed by an obesity specialist or tertiary care center will also be excluded (*e.g*., patients referred for bariatric surgery), as well as patients who are unable to participate in regular clinic visits or programs due to geographic, social or physical reasons.

### Power considerations

The sample size calculation for the patient cohort study is powered based upon the SF-12 and the BMI. For SF-12, a moderate effect size is 0.3, and for a 5% reduction in BMI, a moderate effect size is 0.23 to 0.25. We will aim for 80% power. We will gear our enrolment goal to anticipate a 30% lack of adherence to the complete measurement protocol, ensuring that in this scenario the power will remain reasonable at 70%.

### Procedures: enrollment and data collection visits

Due to ethical and logistical considerations, we were not permitted to randomize directly at the patient level. Thus, we have randomized at the clinic level. We cannot control how many patients enter the evaluation from each clinic, but based on baseline practice size data, we anticipate that there should be balanced representation from 5AsT and control clinics.

Activated patients will be approached for recruitment into the study. Signed informed consent will be obtained at the PCN by trained staff. Patient visits will occur at baseline, 3, 6, 12 and 18 months at the PCN. We will endeavour to have a minimum of 6 months of data on all patients; thus recruitment must end in October 2015 to close the study by end of March 2016. Proposed baseline characteristics of the patients will also be included (Table 3).

**Table 3 T3:** Demographic characteristics and health variables to be collected on patients

Age in years (mean ± SD)	BMI (mean ±SD)
Gender (% female)	Weight status (%):
Ethnic group:	• Overweight:
Caucasian (%)	• Obese:
Attendance to any other weight loss program (%)	o 30-34
Education (%):	o 35-39
	o >40
• High school	Waist circumference (mean ±SD)
• Post-Secondary school	Blood Pressure (mean ±SD)
Income (%):	• Systolic BP
• <$15,000	• Diastolic BP
• $15,000-$29,999	HbA1c (mean ±SD)
• $30000-$49,999	Type II Diabetes (%)
• $50000-$79,999	Hypertensive (%)
• >$80,000	Depression (%)
	Other co-morbidity (%)
	PACIC score (mean ±SD)
Distance to practice (mean±SD)	SF-12 (mean ±SD)
	EQ5D (mean ±SD)

Patient assessment includes: baseline demographics and chronic disease presence (Table 3), measures of self-reported quality of life (EQ5D, SF-12), for follow-up visits a survey on weight management as a chronic disease (modified PACIC, self-report of change behaviour, *i.e*. gym participation, external weight loss programs, number of visits to a healthcare provider for weight management), and measurement of resting heart rate, blood pressure, and basic anthropometric measurements (including height, weight, waist circumferences). We will also monitor compliance with recommended laboratory studies (HbA1c for those with diabetes q 6 months, and for patients over 40 years, fasting cholesterol panel and glucose). If patients are unable to participate in the follow-up in person, a telephone option will be offered. The in-person visit will take 30 minutes per visit on up to five occasions.

### Quantitative data analysis: patient study

Demographic and health variables (Table 3) will be compared using either *t*-test for continuous variables or chi-square test for categorical variables. Main outcome measures are SF-12 and change in weight and BMI. Practice level clustering effects on the secondary outcomes, multilevel models (random effects model) will be considered. Adjustments will be made for individual level characteristics, the random factor (intervention or control practice), nurse and other practice level characteristics. Changes at follow-up will be analyzed using multilevel models with the baseline values as a covariate and to handle missing data [23]. Data modeling is hypothesis-led rather than data-driven, hence all analysis are predetermined. STATA 12 (StataCorp, TX, USA) will be used for statistical analyses.

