### Allocation concealment and randomization

Following ethical approval and study registration, the eligible clinics (N = 24) were allocation concealed and randomized in a 1:1 ratio using a computer generated random sequence by a statistician external to the project. Randomization was stratified for larger vs. smaller patient panel sizes. Three strata with eight practices were created from the 24 eligible practice units. The first 8 units (Group 1) have panel size ≤2,754; Group 2 has clinic panel size from 2,755 to 6,576, and Group 3 has clinic panel size ≥6,577.

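### The patient characteristics in Table 3 are to be compared with t-tests and chi-square tests that ignore clinic randomisation, so they will flag imbalance more often than 5%, by an amount the article does not allow one to fix

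*Protocol article*

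**What the plan says.** The article's section on quantitative data analysis for the patient study opens with the method for Table 3: "Demographic and health variables (Table 3) will be compared using either" a t-test "for continuous variables or chi-square test for categorical variables". No allowance for clinic is attached to that sentence.

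The section on enrolment and data collection visits identifies the table as a baseline table: "Proposed baseline characteristics of the patients will also be included (Table 3". The same section gives the unit of randomisation: "Thus, we have randomized at the clinic level". The section on allocation concealment and randomization gives the number: "the eligible clinics (N = 24) were allocation concealed and randomized in a 1:1 ratio". On patients per clinic, the enrolment section says "We cannot control how many patients enter the evaluation from each clinic".

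The analysis section does recognise clustering, but elsewhere. It says multilevel models will be considered for practice-level clustering in the secondary outcomes. It plans multilevel models for changes at follow-up, with the baseline value as a covariate. It adds that all analyses are fixed in advance.

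**The concern.** Both named tests take each patient as an independent observation. Under the stated design the comparison is between two sets of 12 clinics, and patients of one clinic may resemble each other. Clustering is plausible for some Table 3 items: the practices are described as geographically dispersed, and the table includes distance to practice, income, education and ethnic group. How strongly any of them clusters is not stated.

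What is at stake is how the table is read. In an individually randomised trial a baseline p-value says little. Here patients are recruited after their clinics have been allocated, so a reader will look to this table for signs that the two arms recruited different patients. Tests that ignore clinic give p-values that are too small, so ordinary variation between clinics can look like selection.

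**Working it through.** The article states no error rate, significance level, patient number, patients per clinic or patient-level ICC for this comparison, so there is no figure of its own to reproduce. The check derives a plausible clinic size and then shows the error rate over a range of ICCs.

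**Inputs from the article.** 24 clinics, 12 per arm. Patient-level effect sizes of 0.30 (SF-12) and 0.23 to 0.25 (BMI), with 80% power (power considerations for the patient study).

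**Assumptions.** Two-sided alpha of 0.05; patients spread evenly over the 24 clinics; ICC from 0.001 to 0.10.

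**Step 1, patients per clinic.** Per arm, n = 2(1.960 + 0.842)²/d² = 15.70/d².

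| d | n per arm | Total | Per clinic (total/24) |
|---|---|---|---|
| 0.30 | 175 | 350 | 14.6 |
| 0.25 | 252 | 504 | 21.0 |
| 0.23 | 297 | 594 | 24.75, taken as 25 |

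**Step 2, error rate.** With m patients per clinic, the design effect is DE = 1 + (m − 1) × ICC. A nominal 5% test that ignores clinic rejects a true null with probability 2[1 − Φ(1.96/√DE)]. For unequal clinics, DE = 1 + [(1 + CV²)m − 1] × ICC, where CV is the coefficient of variation of clinic size. A CV of 0.65 is assumed.

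Example, m = 25 and ICC = 0.05: DE = 1 + 24 × 0.05 = 2.20; 1.96/√2.20 = 1.32; rate = 18.6%.

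| ICC | Equal, m = 14.6 | Equal, m = 25 | CV 0.65, m = 14.6 | CV 0.65, m = 25 |
|---|---|---|---|---|
| 0.001 | 5.2% | 5.3% | 5.2% | 5.4% |
| 0.005 | 5.8% | 6.4% | 6.2% | 7.0% |
| 0.01 | 6.6% | 7.8% | 7.3% | 9.1% |
| 0.02 | 8.2% | 10.7% | 9.7% | 13.2% |
| 0.05 | 13.0% | 18.6% | 16.5% | 23.5% |
| 0.10 | 20.2% | 28.8% | 25.6% | 35.3% |

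**Step 3, where the rate doubles.** A rate of 10% needs 1.96/√DE = 1.645, so DE = 1.42. With equal clinics that is ICC = 0.42/24 = 0.0175 at m = 25, and 0.42/13.6 = 0.031 at m = 14.6.

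**Step 4, simulation.** 24 clinics, 3,000 runs per setting. With equal clinics of 25 and ICC 0.05, the t-test and the chi-square test each rejected in 18.0% of runs. With equal clinics of 15 they rejected in 12.9% and 12.3%. Both agree with the formula.

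**Step 5, the alternative.** In the same simulations, a t-test on the 12 versus 12 clinic means rejected in 3.8% to 5.6% of runs, over ICC 0.01 to 0.10 and over equal and unequal clinics of 15 and 25.

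**The case against.** The strongest objections concern size and consequence.

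**Size.** A reader might infer that imbalance will be flagged far more often than 5%. The article does not support that. Without a patient-level ICC or patient number, the excess could be negligible (ICC of 0.005 or less) or several-fold. The only ICC given, 0.40, is for nurses within clinics in the provider study's power calculation; applied here it would give rates of 44% to 55%, but it does not describe patient variables. A reader might also multiply the rate at ICC 0.05 by the roughly 20 variables in Table 3 and predict three to five false flags. That gives every variable the same assumed ICC. In addition, HbA1c is monitored in patients with diabetes, and the modified PACIC is listed for follow-up visits, so these two may not fit that count.

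**Structure.** Patients are eligible whatever clinic they attend, and the network has 46 practices. The number of clusters and their sizes are therefore not fixed, and smaller clusters mean less inflation: with 10 patients per clinic, ICC 0.05 gives 10.4%. In the other direction, enrolment raised for 30% loss could reach about 35 per clinic (594/0.7 = 849; 849/24 = 35.4), with more inflation.

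**Consequence.** The follow-up models are multilevel and adjust for baseline. The article says its analyses are predetermined, and it ties no covariate choice to a Table 3 p-value. An inference that these tests would bias the treatment effect or drive model selection is not supported.

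**Reading.** The sentence on Table 3 says neither baseline nor between arms. That reading is natural but inferred. The expectation that "we anticipate that there should be balanced representation from 5AsT and control clinics" concerns how many patients come from each clinic, so it is not a claim about balance of characteristics.

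All of this stands as a limit on the point. None of it makes the named tests suit the design.

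**Conclusion.** The point holds, with minor severity. The article names tests that conflict with its own unit of randomisation, and its provisions for clustering do not reach the Table 3 sentence. This is a stated choice, so a fuller plan elsewhere does not excuse it as a mere omission.

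The direction is certain for any positive clinic ICC; the size is not. Under the assumptions above (two-sided 5%, 15 to 25 patients in each of 24 equal clinics), the false-flag rate runs from just over 5% at ICC 0.001 to 29% at ICC 0.10, and is higher with unequal clinics. It will differ between variables.

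The harm is confined to interpreting the table as a check on recruitment. A flag is also not necessarily false: because enrolment follows clinic allocation, a real recruitment difference is possible. The planned tests cannot separate that from ordinary variation between clinics.

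**What to change.** In the analysis section for the patient study, delete the t-tests and chi-square tests for Table 3. Present the table by arm with means and standard deviations or percentages, and standardised differences.

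Where a test for differential recruitment is wanted, use one that accounts for clinic: arm in a model with a clinic random intercept, or a comparison of clinic means. Base the degrees of freedom on the number of clinics that actually contribute patients: 24 − 2 = 22 only if all 24 randomised clinics do, and no others. State that the comparison is between arms at baseline, so that the reading no longer rests on inference.

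The cost is a change of wording and a few lines of code. No new data are needed, and the outcome analyses are untouched.

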### Selection of participants for qualitative patient sub-study

At 12 months, a sample of patients who agreed to be contacted will be selected and consented for individual semi-structured interviews. This will address patient-specific experiences of PCN weight management efforts. Purposive sampling will deliberately seek out a wide range of individuals. We will use a pragmatic approach, sampling until thematic saturation is reached. Selection factors will include 5AsT versus control practice affiliation, weight loss success, comorbid medical conditions, and PCN program attendance. Results of the quantitative and qualitative data merge will determine the focus and extent of patient interviews and sub-analyses.

### Qualitative data handling and analysis

Patient interviews will be handled and analyzed using the same techniques and tools as the provider study. The codebook created for the provider study will influence transcript coding.

### Trial status

The 5AsT has been approved by the University of Alberta ethics board and has been registered at Trials.gov (NCT01967797). It is funded by an Alberta Innovates Health Solutions grant.

## Discussion

The 5AsT trial is a theoretically informed, pragmatic trial that uses a multi-level collaborative approach to aim to sustainably change practitioner behaviors to improve obesity management in primary care.

This project is grounded in established theoretical frameworks for behavior change and complex innovations and leverages bi-directional knowledge translation between clinical and academic partners to comprehensively evaluate the implementation of the 5AsT practice change intervention.

Evaluation guided by the RE-AIM framework is particularly useful for determining programs that work in real-world environments [13]. By widening the evaluative focus beyond efficacy, the overall suitability and investment-to-results assessment of the intervention can be made.

As suggested in the conceptual framework of complex innovation implementation Complex Innovations, process is distinct from the evaluation of the 5AsT providers’ behaviour change [11]. We will use a rigorous mixed-methods study design to distinguish issues with implementation process from effectiveness of the intervention. Maximal systemic impact of the research is attained by implementing an integrated approach for sustainability at the outset of the project [24]. Sustainability will be achieved by leveraging existing clinical resources and infrastructure. We will continue to monitor the primary outcome measure for another year post the intervention phase of the project.

### Main findings/messages

This research proposal uses a pragmatic design particularly suited for evaluating the complex, real-world interventions typical of primary care settings [13]. Pragmatic trials measure effectiveness (*i.e*., the degree of beneficial effect in real clinical practice) and are conducted on participants who represent the full spectrum of the population to which the treatment might be applied. It is important to extensively describe the context and population in detail. In addition to the complexity of this research setting, our target patient population (patients who are overweight or obese) constitute one additional level of complexity, given the large variability in the etiology, comorbidity, and drivers of obesity as well as the variable compliance, readiness to change, and treatment preferences. Nevertheless, a key methodological issue in pragmatic trials is finding the right balance between external and internal validity [25]. Provider behaviour is a key feature in any primary care intervention. If providers do not have the skills, beliefs and confidence to be able to intervene effectively with patients, there will not be an improvement in obesity management in primary care. The 5AsT trial aims to understand what provider factors are instrumental to increase the quality of obesity management in primary care.

### Strengths

The strengths of this study are that it is a pragmatic intervention conducted in a real-world setting of a large and diverse Primary Care Network. The mixed methods study design will provide contextual insights into the intervention process and the outcomes. The bidirectional nature of the design of the intervention will ensure relevance to practitioners.

### Limitations

The pragmatic nature of the study design limits the ability to restrict or steer patients’ access to programming within the system, resulting in possible imbalance between practice contributions to the patient cohort. Furthermore, the dynamic and evolving clinical environment may result in shifting context and priorities within the network over time. Generalizability to other primary care networks and practitioners may require further adaption and intervention strategies tailored to those settings.

### Summary

The 5AsT trial addresses a need for knowledge exchange around obesity management in primary care in a practical and sustainable format geared towards real-life situations. The use of existing resources, collaborative design, practice facilitation, and integrated feedback loops cultivate an applicable, repeatable and adaptable approach to increasing the quality and quantity of primary care weight management visits. Its mixed method design will provide rich material to evaluate intervention effectiveness. A comprehensive 5AsT intervention implementation plan will address identified key barriers to obesity management in primary care.

## Abbreviations

CON: Canadian Obesity Network – Réseau Canadien en Obésité (CON-RCO); FTE: Fraction of a full time (1.0) appointment held by a practitioner (*i.e*., 0.5 is half time); Panel: Number of patients affiliated with a primary care practice; PCN: Primary care network; RN: Registered nurse; ESPCN: Edmonton south side primary care network.
